### The intervention

The PHISICC paper-based intervention is a full set of paper-based tools to support decision making by front-line HW. These are the only tools to be used by HW in the intervention arm. The PHISICC tools encompass the whole system (ie, recording and reporting) and all clinical and public healthcare areas and are characterised by a common visual language (eg, spaces for digits and text), and standardised formats across healthcare areas. To support front-line HWs decision making, the PHISICC tools incorporate specific places to explicitly record critical data items (eg, respiratory rate in infants), graphic artefacts to distinguish severity degrees of signs or symptoms (ie, small square for ‘normality’, diamond for ‘attention’ and bold diamond for ‘critical severity’); space to document diagnoses and treatment decisions; and aides memories in the first page of register books.

The PHISICC tools have been developed from May 2017 till June 2019, including production, using a HCD approach.^12^ A strength of the HCD approach is its ability to unlock the user’s perspective so that designers can build solutions that are fully reality-based and work well. Cocreation groups were formed in each country with researchers, staff from partner institutions and healthcare workers, led by a team of professional designers. Research team members supervised and coordinated exclusively the feedback on the contents of the tools, to ensure compliance with each country clinical guidelines. At the outset of the process, the design focused on three healthcare areas (ie, antenatal care, vaccination and sick child) and slowly extended the new visual language to other healthcare areas. Initial workshops served to brainstorm on problems and potential design solutions, without any other rule than being comprehensive and not rejecting a single idea. Designers, then, formalised some of the most promising solutions and a first round of exchanges within the cocreation team was used to address misinterpretations or inconsistencies. There were two in-the-field testing rounds in Mozambique, two in Côte d’Ivoire and three in Nigeria and uncountable exchanges through teleconferences and email, in-between. The prototypes were considered final when no errors were detected, were compliant with data needs in each country and comments from the field could not be accommodated in the design concept or there was no consensus on minor or formal issues being raised.

The PHISICC tools have been produced in French for Côte d’Ivoire, in Portuguese for Mozambique and in English for Nigeria, which are the official languages used in the health systems in the three countries. They include the official logo of the MOHs. Healthcare areas covered include: family planning, antenatal care, including tetanus toxoid vaccination, delivery, postnatal care, vaccination, sick child, adults outpatient consultation, tuberculosis diagnosis and treatment, and HIV. Referral forms were also designed.

The PHISICC tools have three subcomponents: registers, tallies and reports. Registers are formed by seven Deutsches Institut für Normung (DIN) -A3 and one DIN-A4 (for referrals) book covering all healthcare areas except for tuberculosis treatment, for which DIN-A3 cards where used. Register books have 100, 200 or 400 pages depending on the country and healthcare area. They are used to record individual clients’ data for each healthcare event, either of clinical or public health nature. Some register books have clinical notes at the very beginning, as ‘aide memoires’, and an example of a filled-in form, to assist HW when doubting how to proceed.

Tallies are DIN-A3 single sheets which contain a list of the indicators to be transferred to higher levels of the health system, with a series of small ovals, grouped in fives, to mark with tally sticks with a pen. In contrast to the current systems that have no tallies or only for vaccination, tallies were created for all healthcare areas. In the middle-right side of the tally, a column accommodates cells aligned with the ovals to insert the count for each indicator; and in the far right of the sheet there is a replica of the count column, separated with a perforated line, which is detached and sent, as part of the monthly report to the higher level in the health system.

While current HIS tools are consistently organised in tabular formats and books, where each clinical event is recorded in a row and each variable (eg, age, gender, HIV status, diagnosis) in a column, PHISICC tools incorporated several innovations; in summary: a visual language to guide the clinical decisions of HWs based on severity (ie, if it is recorded that a child has convulsions, a visual artefact indicates severity), more space for clinical data (eg, vital signs), inclusion of all critical information to assess patients (eg, obstetric history, gestational age, fundus height, breath rate in infants), consolidation of information of all antenatal care visits for a single pregnant woman in the same page, among many other formal and contents improvements, including improved aesthetics. A systematic comparison of the new (intervention) and current (control) tools is provided in table 1.

**Table 1 T1:** Comparison of new (intervention) and current (control) tools

Characteristics	New (PHISICC intervention) tools	Old (control tools)
Development approach	Human-centred design, cocreation with users	Centrally done, based on data and information experts
Visual language	Standardised across tools	No visual elements
Information structure	Following clinical processes	Tabular form, following reporting requirements
Decision aids	Icons representing mild, moderate and severe conditions	Not available
Register books layout	Landscape, DIN-A3	Depending on healthcare area; often much larger than DIN-A3
Tally sheets to aid counting events	For each healthcare area, to be filled as healthcare events take place	Only for vaccination, to be filled as vaccinations take place
Reporting	Integrated with tallying/counting	Requires revisiting register books at the end of the month

DIN, Deutsches Institut für Normung; PHISICC, Paper-based Health Information System in Comprehensive Care.

We aimed at creating ‘a system’ (not just some tools) focusing on decision making by front-line HWs. The epidemiological and public health contexts in the three countries are similar, as confirmed by the similarities in the existing HIS between the three. The visual language and the recording forms where common to the three countries because clinical decisions are common to the three; although forms allowed for specific tests or treatments. The reporting component was adapted to each country set of indicators, although the visual language and reporting processes were harmonised.

During 3 or 4 days, HWs were trained on HIS before the start of the trial. In the intervention arm they were trained on the PHISICC tools; and the control arm received a refresher training about the regular tools, during the same number of days.

Additionally, given that the regular tools already contained information on past vaccination history of children still to complete their vaccination schedule, we created a mechanism to retrieve data of children’s vaccination status to transcribe into the new vaccination register book in the intervention arm (‘system transition’).

Tools were endorsed by MOH, printed in local printing companies and distributed to HW at the end of the training sessions. A digital spreadsheet was created to monitor consumption and order additional tools to cover health facility needs during the life of the trial.

### Outcomes

There are five primary outcomes (table 2). Vaccination adherence is defined as the total number of vaccine doses given in the correct time interval to children in households in the HFs catchment villages over the total number of vaccine doses that should have been given during the same period. Antenatal care visits uptake will also be considered depending on the expected number of pregnancies in the study areas. Both are used as proxies for health outcomes in terms of protection against disease^13^ and prevention of pregnancy complications^14^ and are assessed in a random sample of households in the HFs catchment areas. Data concordance is defined as the level of agreement of HIS indicators between (1) records of healthcare events (recounts), (2) tallies (recounts) and (3) reports (aggregated data to higher levels of the system).^3^ Decision making will be assessed considering the diagnostics scope in the sick child (ie, number of different diagnoses per sick child consultation) and treatment appropriateness (ie, number of prescribed treatments that are supported by a documented diagnosis). These outcomes will be assessed in a random sample of records and corresponding reports during the last 4 months of the study period. HWs satisfaction will be assessed in all HWs in included HFs using a standardised questionnaire.^15–17^ While the intervention targets HF, some of the outcomes are measured at the level of HF and some others in the communities of HF catchment areas.

**Table 2 T2:** Outcomes and parameters used to estimate the sample sizes

	Outcome name	Subjects	Definition	Baseline estimate	Expected change	Comments
1	Vaccination adherence	Children under 1 year (sample of households in catchment areas)	Number of vaccines given in the previous calendar year over the number of vaccine due in the same period	75 given per 100 due	Increase of 10 per 100	Vaccines are clustered within children, and children within HFs
2	Data concordance	Recording tools in health facilities (samples of records)	Number of healthcare events (eg, vaccinations, antenatal care consultations) recounted in the previous calendar year vs the number of healthcare events reported in the same time period	Seven recounted for each 10 reported^3^	Increase of 1 recounted	A single estimate can be obtained in each HF or by time periods (no clustering)
3	Diagnostic scope	Records of sick child consultations (samples of records)	Number of diagnosis in each sick child consultation during the previous calendar year	30% with more than one diagnosis	35% with more than one diagnosis	Individual consultations are clustered within HF
4	Treatment appropriateness	Records of sick child consultations (samples of records)	Number of treatments correctly prescribed in each sick child consultation during the previous calendar year	Half appropriate over all consultations	Increase to 60%	Individual consultations are clustered within HF (one treatment per child)
5	Health workforce satisfaction	Health workers (all health workers form include health facilities)	Degree (score) of satisfaction with the HIS across all health facilities in each arm	50% satisfied	75% satisfied	More than one health workers can be approached in each HF

HF, health facility; HIS, Health Information System.

Secondary outcomes are classified under the following domains: data quality, data use, mortality, HW experience, client experience and resource consumption:

Data quality, assessed in a sample of recordsCompleteness of recording and reporting in specific forms; that is, prevalence of unduly missing data items, partograph used.Accuracy of recorded figures in comparison to real events (eg, physical counting of commodities, such as number of 500 mg paracetamol tablets as recorded versus number of 500 mg paracetamol tablets as counted).Timeliness of reporting, as documented by time stamps in forms.Loss of data or data which does not reach the next upper administrative level.Data use, assessed in a sample of recordsIn terms of knowledge (eg, vaccines due based on date of birth; weight for length assessments).Cases of different conditions properly treated (eg, diarrhoea cases given oral rehydration therapy according to national guidelines; pneumonia cases given appropriate antibiotic according to national guidelines).Public health decisions: availability of lost to follow-up lists or plans for vaccination, tuberculosis or HIV/AIDS treatment control.Occurrence of stock outs of essential drugs.Overall under-5s mortality and under-5s mortality excluding perinatal mortality,^18^ in a sample of households in HFs catchment areas.HWs’ ‘human experience’ and satisfaction (all HWs).District health information officers’ ‘human experience’ (selected healthcare programme managers).Clients’ ‘human experience’ and satisfaction, in a sample of households in HFs catchment areas.Resources consumption (eg, time use, costs)Intervention costs: tools, training, start-up.Time used for recording and reporting (eg, time-motion study).^19^Cost-effectiveness per unit of additional improvement in outcomes of interest.

It is worthwhile to note that outcomes that do not relate to data quality and use will be assessed using additional data collection tools (eg, survey questionnaires), which are the same for intervention and control HFs. Hence, the effects of the intervention cannot be attributed to the changes in performance of the paper tools routinely used to record healthcare events in intervention and control HFs, which are different by design.

In addition, we will consider ‘explanatory outcomes’ that will help to understand how the measured effects have taken place and why. We will look at the details of the interplay between the intervention, the system, the users and the context. Process indicators will be based on the documented activities that have taken place, from the conception of the intervention, up to its implementation, monitoring and evaluation. Process indicators may include: intervention setup and implementation, monitoring of the use of the intervention, special activities targeted at vulnerable populations, district reactions related to the intervention, handling of data coming from the new system, sustainability based on costs information and perceptions, alignment with national health policies and donor priorities. We will also explore healthcare services characteristics looking at generic indicators from HFs, such as human resources profiles and relations with the communities, population characteristics and system and context characteristics captured in early stages of the project, where data are available.

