### Allocation and blinding

Allocation of HF into the intervention and control arms took place in a formal event, gathering research partners and MOH officials to offer transparency and promote study ownership by local and national authorities. Equally sized, folded pieces of paper with the names and codes of included HF written on them were introduced in an opaque receptacle where they were manually and blindly mixed. A second receptacle contained two equally sized pieces of paper, one with the word ‘intervention’ and another one with the word ‘control’. A selected person in the meeting, not belonging to the research team, extracted one piece of paper at a time to reach half the number of included HF. Then, a paper was extracted from the second receptacle to assign those HF to the intervention or control arms. The rest of the papers were extracted as well to verify completeness and no duplication of names, and those HF were assigned to the other arm.

Once HFs were selected, all villages or settlements for each health facility catchment area were listed and three in each catchment area were selected. In practice, we selected all villages because the numbers were below (in Côte d’Ivoire) or just above (in Nigeria) the needs. For each village, we used Google satellite maps to identify and geo-locate every visible roof. Where there were many houses per village (roughly, more than fifty or so), a researcher would mark four points in the map slightly beyond the northernmost, southernmost, easternmost and westernmost roofs seen and 30 random points were selected within that square. From the mapped points, 10 per village (with 20 more acting as reserve) were randomly selected and marked on another map used in the field for data collectors to approach households. Where technical problems impeded this approach in a given village, a field supervisor would rotate a bottle on the floor towards the centre of the village and would select at random 10 households in the direction pointed by the bottle, from the outer limit of the village till the centre.^11^

Blinding is only feasible for the research team members carrying out the CRCT data collection and the analyses of the CRCT findings. The intervention (ie, paper tools) are by design very different from the existing system and it is not possible to blind participants or principal researchers.

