### Sample size calculations

The required sample sizes for each primary outcome were determined using simulation to incorporate the clustering (table 1) and to take the baseline and end-line surveys into account. Briefly, we simulated 1000 trials with variation between them caused by drawing different samples from the same distributions. We then used the regression models detailed in the data section to analyse each of the simulated trials and estimate the power as the proportion of trials which detected the effect of the intervention as significant. The simulation code was written in R (online supplemental files 2 and 3).

10.1136/bmjopen-2021-051823.supp2Supplementary data

10.1136/bmjopen-2021-051823.supp3Supplementary data

For each country, we require the probability of α, a type I error (rejecting the null hypothesis when it is actually true) to be less 0.05 and the power to be at least 80%.

For vaccination adherence, using a sample size of 35 HF per arm, we would have 80% power in each country to detect as significant a difference between a proportion of due vaccines given from 75% in the control to 85% in the intervention arms, assuming one child per household, 30 households per HF and a between-HF variation equivalent to a k of 0.25, where k is equal to the SD divided by the mean. The value of k is unknown, but was chosen in line with general observations by Hayes and Bennett.^20^

For data quality outcomes, with 35 HF per arm we would be able to detect as significant a difference from a ratio of 0.7 (reported:recorded) vaccinations in the control arm to 0.8 with the intervention with 80% power, assuming 100 recorded vaccinations per HF and an SD of 0.25 in the ratios between HF.

In terms of diagnostic scope, we would be able to detect an increase in the proportion of child visits with more than one diagnosis from 30% to 35% with 80% power with 35 HF per arm, 60 records per HF and assuming a k of 0.25.

We would be able to detect as significant an increase from 50% of treatments having a corresponding appropriate diagnosis to 60% with 80% power assuming 35 HF per arm, 1 treatment per child, 25 children per HF and variation between HF corresponding to k=0.25.

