### Measures to minimise bias

Statistical analyses will be carried out blindly, without knowledge of what HFs or population in the catchment area belong to the intervention or control arms. Only when the analysis code is considered as definitive and fixed, will results be shared with the wider investigators team and the arms for HFs and population will be disclosed.

Outcome measurement bias may take place where data from the HIS, which is the focus of the intervention, is used to measure outcomes. However, we will minimise this by assessing population based outcomes at household level.

Contamination (ie, the intervention affects individuals or units assigned to the control arm) may happen via the exchanges between HWs from HFs in both arms; for example, in monthly district data quality meetings, managerial meetings; or through inputs from supervisors who influence control HFs with intervention tips encountered in HFs of the intervention arms. One mechanism to address this issue is using a district-based cluster randomisation scheme. However, we consider that (1) contamination, despite increasing the awareness of health works in control HFs, will hardly influence the decision making mechanisms that the HIS intervention focuses on and (2) randomisation at the level of district poses additional challenges that are not worth the marginal benefit of reducing a doubtful contamination.^32^

The spill-over effect (ie, benefits of the intervention extend beyond their direct recipients)^33^ may take place in higher levels of the health systems; for example, district data managers and programme managers may experience the benefits of better structured and more timely data produced in HFs in the intervention arms. The trial will have no capacity to quantitatively account for spill overs at higher levels of the system, due to the limited number of higher level administrative areas that will be involved in the trial. However, through process indicators, we will consider potential benefits and harms of the intervention at higher levels of the system.

A challenge is the Hawthorne effect (ie, observer effect). Both HWs in the intervention and in the control sites will have an awareness of being observed as data collection activities will be at the same level of intensity in the two arms. Therefore, there should be no differential effect.

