Analyses will be based on the intention to treat. It is important to closely monitor if the intervention HFs consistently use the new HIS tools and approaches. The data collection team and the trial monitoring team will check if old forms are still being used in the intervention HFs. However, we do not expect HFs to migrate between intervention and control arms, or vice versa, due to feasibility issues. On the other hand, some household members in a given catchment area may decide to seek for healthcare in a health facility belonging to another trial arm. In these cases, households will be analysed as belonging to the original trial arm.

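### Diagnostic scope and treatment appropriateness are read from registers that in one arm are the intervention, so alone they cannot separate better recording from better decisions

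*Protocol article*

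**What the plan says.** All references are to the protocol article.

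- **Outcomes and Table 2.** Diagnostic scope (number of diagnoses per sick child consultation) and treatment appropriateness are primary and are introduced as the assessment of decision making. Both come from samples of facility records. Outcomes defines appropriateness as the "number of prescribed treatments that are supported by a documented diagnosis"; Table 2 and Data analysis speak instead of treatments being correctly prescribed.
- **The intervention.** The PHISICC tools are the only ones used in the intervention arm. Among their features is "space to document diagnoses and treatment decisions". The same section says that current tools are tabular and names diagnosis as one of their columns.
- **Allocation and blinding.** Facilities received the tools shortly after baseline data collection. "Blinding is only feasible for the research team members carrying out the CRCT data collection" and for the analyses, although the tools are said to look very different from the existing ones.
- **Data analysis.** For outcomes measured at both surveys, the effect is the interaction of arm and survey.
- **Measures to minimise bias.** Measurement bias is acknowledged where outcomes come from the health information system. The answer given is: "However, we will minimise this by assessing population based outcomes at household level". Later in the section: "The data collection team and the trial monitoring team will check if old forms are still being used in the intervention HFs".
- **Ethics and dissemination.** The household survey in Mozambique was cancelled.

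**The concern.** A diagnosis that is made but not written counts as not made, and the treatment that went with it counts as unsupported. Both outcomes therefore depend on what the health worker decides and on what the form leads the health worker to write. The form differs between arms at end-line because the form is the intervention. A difference between arms could come from decisions, from recording, or from both, and these two outcomes alone cannot say which.

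Better recording is a legitimate effect of the tools if it is reported as recording. The risk lies in the label. The trial is meant to inform policy, and a positive result on a decision-making outcome could be read as better care for sick children when only the writing had changed.

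**Working it through.** **1. The plan's own figures.** The plan requires, per country, a type I error "to be less 0.05 and the power to be at least 80" per cent. Diagnostic scope is planned for a change "from 30% to 35% with 80% power with 35 HF per arm, 60 records per HF and assuming a k of 0.25". Treatment appropriateness is planned for "an increase from 50% of treatments having a corresponding appropriate diagnosis to 60% with 80% power assuming 35 HF per arm", with 25 children per facility, one treatment each and k = 0.25.

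An approximate check uses a difference in differences with a stable facility effect that cancels:

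power = Φ(√(35·d² / v) − 1.96), where v = (3·p0·q0 + p1·q1)/n and q = 1 − p

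- Diagnostic scope: v = (3 × 0.21 + 0.2275)/60 = 0.01429; √(35 × 0.0025/0.01429) = 2.47; power 0.70 two-sided (0.80 one-sided).
- Treatment appropriateness: v = (3 × 0.25 + 0.24)/25 = 0.0396; √(35 × 0.01/0.0396) = 2.97; power 0.84 two-sided (0.91 one-sided).

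Simulation of facility-level change scores (4,000 trials) gave 0.68 to 0.70 and 0.83 to 0.87 two-sided. No single convention tried gave 80% for both outcomes. The plan's simulation code is in supplements not shown here, so its power figures are not called wrong. The formula is used below only as a yardstick.

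**2. Does the interaction remove a recording shift?** At baseline both arms use the old tools, so p0 applies to both. At end-line suppose care is unchanged and only recording moves, in the intervention arm. For appropriateness, (0.60 − 0.50) − (0.50 − 0.50) = 0.10. The whole shift is in the interaction. Baseline adjustment removes stable differences between facilities, not an instrument that changes in one arm.

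**3. How large a shift would match the planned effect?** Let f be the share of records not counted at p0 that become counted because a diagnosis is now written: p1 = p0 + (1 − p0)·f.

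- Diagnostic scope: f = 0.05/0.70 = 7.1% of records that otherwise show one diagnosis or none.
- Treatment appropriateness: f = 0.10/0.50 = 20% of treatments that otherwise lack a written supporting diagnosis.

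The documents give no documentation rate, so f is an assumption. The chance of a two-sided significant result from recording alone is:

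| f | Diagnostic scope (60 records) | Appropriateness (25 records) |
|---|---|---|
| 5% | 41% | 11% |
| 7.1% | 70% | 18% |
| 10% | 93% | 32% |
| 15% | over 99% | 60% |
| 20% | over 99% | 84% |
| 25% | over 99% | 96% |

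The sample size summary asks for 60 sick child records per facility. If appropriateness were read from all 60, the entries at f = 10% and 15% would be 63% and 93%.

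**4. The opposite direction.** The new forms also give space for treatments. Suppose g more treatments without a written diagnosis are recorded per 100 now recorded, with 50 supported. The proportion becomes 50/(100 + g), and g = 25 gives 50/125 = 40%, a fall of 10 points. Combined with f = 20%, 60/(100 + g) returns to 50% at g = 20. The sign of the net shift is therefore open.

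**5. Does the stated safeguard reach these outcomes?** Neither is a household outcome. The assurance in Outcomes about identical instruments in both arms is limited to outcomes other than data quality and use. In Mozambique there is no household survey, so vaccination adherence, the primary outcome taken from that survey, is not available as a counterweight there.

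**6. Blinding.** A collector who reads a register sees which form it is. A team that checks for old forms in intervention facilities must know which facilities those are. The arm codes A and B described under Data collection and management mask the analyst, not the person at the register.

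**The case against.** The strongest reply is that the plan is open about the problem. It names measurement bias from using system data, it says in the definition that the diagnosis must be documented, and it limits its same-instrument assurance. It also plans completeness of recording, accuracy checks and explanatory outcomes, which would help a reader interpret a recording shift. Both arms had training of equal length, so training time does not differ. All of this stands. It means that the fault is a safeguard that misses these two outcomes, not silence about the risk.

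Three stronger readings are tempting and are not supported:

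- *That PHISICC adds a diagnosis field which control registers lack.* Current tools have a diagnosis column, and Table 1 does not list this as a difference. What is documented is a difference in layout, space and prompting, of unknown size.
- *That recording will produce the planned effect.* The values of f are hypothetical, and step 4 shows that appropriateness could also be pushed down.
- *That collectors judge appropriateness with the form in view.* The article does not say who applies the rule or when. Collectors may only abstract, with classification done later on coded data. What the documents show is that collectors see the forms.

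Restricting the analysis to the first-listed diagnosis would not help: diagnostic scope is planned as the share of consultations with more than one diagnosis, which would then be zero in both arms.

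**Conclusion.** The point holds as one of interpretation and labelling, plus one contradiction. As defined, the two outcomes measure what is documented, on an instrument that changes after baseline in the intervention arm only, and the stated mitigation does not cover them. Shifts of about 7% (diagnostic scope) and 20% (appropriateness) in the records not otherwise counted would equal the planned differences with no change in care. This rests on the plan's own 30% and 50% starting values and on hypothetical recording shifts whose true size and direction are unknown. It does not show that the trial's result will be an artefact.

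Separately, the statement that collectors can be blinded conflicts, for record-based outcomes, with the visibly different forms and the old-form check. The two definitions of appropriateness are also different constructs and need to be reconciled.

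**What to change.** 1. Define and report the two outcomes as documented diagnoses and treatments supported by a documented diagnosis. State that they cannot alone separate better recording from better decisions, and rest claims about care on tool-independent outcomes where these exist. For Mozambique, say plainly that the household outcomes are absent.
2. Reconcile the two definitions of appropriateness. Apply one rule centrally, by code, to abstracted diagnoses and treatments with arm and form type removed, and in the same way to baseline and end-line data so that the interaction is not distorted. This protects against knowledge of arm when classifying; it does not remove differential recording, so item 1 is still needed.
3. Limit the blinding statement to analysts, and to collectors only for outcomes not read from the registers.
4. Interpret both outcomes alongside the planned completeness-of-recording outcome, noting that it is read from the same registers.

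The cost is a narrower headline claim, some rewording and a small coding task. If baseline abstraction kept only a final classification and not the underlying entries, which the article does not say, item 2 would also need those baseline records to be abstracted again. No new facilities or change of design are needed.
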